#### Contraindication to receiving high-flow nasal therapy

Nasal obstructionPrevious bleomycin administrationBase of skull fracture

### Study procedures

The Pre-SAFEx study design is summarised in Fig. 1 and described in detail below and in Table 1.

**Fig. 1 Fig1:**
[figure not shown]
Pre-SAFEx trial flow chart

**Table 1 Tab1:** Participant timeline and schedule of assessments

Study procedure	Visit 1 (Pre-Screen)	Visit 2 (Provision of Patient Information Leaflet)	Visit 3 (Formal screening, answering questions & taking consent)	Visit 4 (Randomisation and undertaking of study)	Visit 5 (Assessment of recovered capacity and taking consent)	Visit 6 (Undertaking Questionnaire)
Assess if patient meets the entry criteria (Pre-Screen)	✓					
Give verbal and written information to • The patient OR • Next of kin (Nearest Relative/Guardian or Welfare Attorney (Scotland)) or nearest ward if no suitable Nearest Relative/Guardian or Welfare Attorney (Scotland) is available		✓				
Assess if patient meets the entry criteria (Formal Screen)			✓			
Patient consented to the study			✓			
Final assessment of eligibility criteria (Cross referenced with medical records)			✓			
**Patient randomised to one of 2 groups:** **Group 1:** • EIT applied and recording commenced 15 min prior to planned extubation • HFNT running at least 10 min prior to extubation. (HFNT will be administered via *Fisher and Paykel Airvo 3* with *Optiflow DUET* nasal cannula) • Start at 10 L/min flow and FiO2 of 0.4 with the cuff of the endotracheal tube inflated—increasing the flow rate gradually to a maximum rate 60L/min or as high as can be tolerated by the patient. At 5 min before extubation, the flow rate should be either at 60 L/min or as high as can be tolerated by the patient. Record the maximum flow that is tolerated by the patient • Endotracheal, infraglottic and supraglottic suctioning prior to extubation • Cuff let down and immediate extubation with simultaneous application of HFNT • 10 min after extubation, FiO2 weaned in a protocolised manner to 0.21 – or as close to 0.21 as possible over 25 min • If successfully weaned onto room air, the flow rate of HFNT is reduced in a protocolised manner over 120 min: 60 min at 60L/min (or highest flow rate tolerated) and 60 min at 30L/min • End of weaning protocol **Group 2:** • EIT applied and recording commenced 15 min prior to planned extubation • Endotracheal, infraglottic and supraglottic suctioning prior to extubation • Cuff let down, patient extubated on to low-flow conventional oxygen with an FiO2 up to 0.4 and then the patient will be weaned at the discretion of their clinician over 2 h and 35 min • End of weaning The electrical impedance tomography/saturation measurements will last in total for 2 h 50 min (15 min before and 2 h 35 min after extubation). After this period, the patient can remain on either HFNT or low-flow oxygen and weaned at the discretion of the treating clinician At an appropriate time after the weaning protocol, patients from both groups will be asked to complete a Visual Analogue Scale Questionnaire exploring the Acceptability and Tolerance of the allocated Oxygen Delivery Device (HFNT or COT) and that of EIT recording. The patient will be followed up at 24, 48 and 72 h post-extubation for any incident of repeat intubation. The study will then conclude at 72 h post-extubation				✓		
**Data collection and time points** ***Baseline data*** Patient details: age; gender’ presumed or actual diagnosis; chest hemi-diameter; height; weight Ventilator settings: ventilation mode; pressure support settings; FiO_2_ Physiological parameters: respiratory rate; oxygen saturation; heart rate; blood pressure ***Pre-extubation*** **Parameters within 1 h prior AND 15 min prior to planned extubation (*15 min prior only):** Ventilator settings: (as above) Physiological parameters: (as above) EIT parameters*: EELZ; ΔZ ***Parameters within 15 min pre-extubation*** HFNT settings: FiO_2_; flow rate Ventilator settings: (as above) Physiological parameters: (as above) EIT parameters: (as above) ***Extubation*** Type of oral endotracheal tube ***Post-extubation (2 h 35 min)*** **SAFEx group** HFNT settings (as above) **COT group** Details of oxygen delivery device **All groups** EIT parameters (as above) Physiological parameters (as above) ***Post-extubation (0–72 h)*** Reintubation rate: 24, 48 and 72 h Visual Analogue Scale Questionnaire exploring • The Acceptability and Tolerance of the allocated Oxygen Delivery Device (HFNT or COT) • The Acceptability and Tolerance of EIT recording				✓		
**Recovered capacity** Should the patient demonstrate Recovered Capacity, they will be provided with verbal information and a separate Patient Information Leaflet before being invited to give their written consent for ongoing study participation					✓	
**Undertaking Questionnaire** Visual Analogue Scale Questionnaire exploring • The Acceptability and Tolerance of the allocated Oxygen Delivery Device (HFNT or COT) • The Acceptability and Tolerance of EIT recording						✓
Reporting of ***adverse events*** or ***serious adverse events***				✓	✓	✓

#### Randomisation

After providing consent, eligible patients will be randomised in a 1:1 manner using a computer-generated 30 number sequence of ‘1 s’ and ‘2 s’ from https://www.random.org/ between (1) SAFEx treatment and (2) standard care. A clinician not involved in the study will obtain this 30 number sequence and conceal its order within 30 sealed, opaque, numbered envelopes. Participants will be unblinded to the research team following randomisation.

Participants will be randomised to one of two groups:

### Group 1 (SAFEx)

*Enlight 2100* electrical impedance tomography system will be applied and recording commenced 15 min prior to planned extubation.HFNT commenced at least 10 min prior to extubation. (HFNT will be administered via Fisher and Paykel *Airvo 3* with an *Optiflow DUET* nasal cannula.)Starting at 10 L/min flow and an FiO_2_ of 0.4 with the cuff of the endotracheal tube inflated, the flow rate will be gradually increased to a maximum rate of 60 L/min or as high as can be tolerated by the participant. Five minutes before extubation, the flow rate should be either 60 L/min or as high as can be tolerated by the participant. The maximum flow that is tolerated by the participant will be recorded.Endotracheal, infraglottic and supraglottic suctioning undertaken prior to extubation.The endotracheal cuff will then be let down and immediate extubation performed with simultaneous application of HFNT.Ten minutes after extubation, FiO_2_ will be weaned in a protocolised manner to 0.21 or as close to 0.21 as possible over 20 min.If successfully weaned on to room air (FiO_2_ 0.21), the flow rate of HFNT will be reduced in a protocolised manner over 120 min: 60 min at 60 L/min (or the highest flow rate tolerated) and 60 min at 30 L/min.End of weaning protocol

### Group 2 (standard care)

*Enlight 2100* electrical impedance tomography system will be applied and recording commenced 15 min prior to planned extubation.Endotracheal, infraglottic and supraglottic suctioning undertaken prior to extubation.The endotracheal cuff will then be let down and immediate extubation performed on to low-flow conventional oxygen with an FiO_2_ up to 0.4The participant will then be weaned at the discretion of their clinician over a maximum of 2 h and 30 min to mirror group 1End of weaning

An unsuccessful wean is defined as an oxygen saturation of ≤ 93% and a respiratory rate ≥ 31 for longer than 30 s in total within a 5-min interval. Immediately after an unsuccessful wean occurs, the FiO_2_ will be increased by 0.1 to prevent continued desaturation and the study will be stopped.

The study will also be stopped for any of the following reasons: heart rate ≥ 150 bpm at any point; systolic blood pressure ≤ 70 mmHg when recorded at 5-min intervals; SpO_2_ ≤ 88% at any point; or respiratory rate ≥ 40 bpm at any point or there is clinical concern at any point. Clinicians will be able to institute rescue therapy at their discretion. This may include fluid boluses, increasing the flow rate, FiO_2_, non-invasive ventilation or intubation.

The electrical impedance tomography/saturation measurements will last for 2 h 45 min (15 min before and 2 h 30 min after extubation). After this period, the participant can remain on either HFNT or low-flow oxygen and be weaned at the discretion of the treating clinician.

At an appropriate time after the weaning protocol, participants from both groups will be asked to complete a visual analogue scale questionnaire exploring the acceptability and tolerance of the allocated oxygen delivery device (HFNT or COT) and that of EIT recording. The participant will be followed up at 24, 48 and 72 h post-extubation for any incidence of repeat intubation. The study will then be concluded at 72 h post-extubation. 

### Data collection and time points

A participant timeline and schedule of assessments is summarised in Table 1.

### Assessment and measurement

Baseline assessment will include demographic characteristics: age, gender, presumed or actual diagnosis, chest hemi-diameter, height and weight.

The primary feasibility outcome will be the recruitment rate to the study protocol over 12 months with a 1:1 randomisation of patients between SAFEx treatment and standard care. The associated endpoint will be the average rate of recruitment per month over 12 months (with a set upper limit of 30 patients recruited over 12 months, i.e. a recruitment rate of 2.5 patients per month).

The secondary outcomes (including additional measures of feasibility together with clinical and exploratory outcomes) are summarised in Table 2 with their associated outcome measures.

**Table 2 Tab2:** Secondary outcomes and associated end points in the Pre-SAFEx study

Secondary outcome	Associated endpoint
The feasibility of a SAFEx treatment model peri-extubation using HFNT	The failure rate of the procedure defined as the proportion of patients in whom SAFEx treatment could not be tolerated
The safety of a SAFEx treatment model peri-extubation using HFNT	The incidence of Adverse Events (AEs) and Serious AEs (SAEs) associated with SAFEx treatment
The tolerability of a SAFEx treatment model peri-extubation using HFNT	Patient Visual Analogue Scale scores for questions exploring the tolerability of SAFEx treatment compared with that of standard care. Patients will be asked to rate their experience with the oxygen delivery device they were randomised to for: • Overall comfort • Perceived dyspnoea • Ability to speak • Ability to hear • Ability to clear secretions • Sensation of bloating • Sensation of dry mouth • Sensation of nasal dryness • Fear **and** Withdrawal rate from the study due to inability to tolerate the trial procedure
The rate of completion of the SAFEx weaning protocol	Defined as the percentage of patients who completed the weaning protocol without breaching any of the physiological patient safety criteria **and** The average fraction of inspired oxygen and oxygen flow rate administered in each group before desaturation occurred
The feasibility of impedance measurement in intubated and ventilated patients using the *Enlight 2100* Electrical Impedance Tomography system	The failure rate of the procedure, defined as the proportion of patients in whom impedance data cannot be measured
The safety of impedance measurement using the *Enlight 2100* EIT system	The incidence of Adverse Events (AEs) and Serious AEs (SAEs) associated with impedance measurement
The tolerability of impedance measurement using the *Enlight 2100* EIT system	Patient Visual Analogue Scale scores for questions exploring the tolerability of impedance measurement: Patients will be asked to rate their experience with EIT for: • Overall comfort whilst wearing EIT • Overall comfort on removal of EIT • Overall ease of breathing with EIT **and** Withdrawal rate from the study due to inability to tolerate the trial procedure
The change in global impedance in patients randomised to the SAFEx treatment pathway or COT	The change in EELZ and ΔZ measured pre and post extubation
The reintubation rate	The rate of repeat intubation at 24, 48 and 72 h post-extubation

### Data analysis plan

#### Baseline assessment including demographics

The data will be analysed using a standard statistical package. Demographic and clinical characteristics of the sample will be examined descriptively (mean, standard deviation, percentage) to examine the size of each group and to account for the imbalances between the two groups.

#### Primary feasibility and acceptability data analysis

The feasibility parameters and progression criteria for success are outlined in Table 3 and will inform the design of a subsequent larger multi-centre feasibility trial evaluating our SAFEx protocol. If all or some of the progression criteria are not met, investigators will examine contributing factors to feasibility findings and pursue modifications as needed to the study and its delivery prior to any subsequent larger trial.

**Table 3 Tab3:** Feasibility parameters

Parameter	Data Collection Methods	Criteria for Success
Recruitment Rate	Number of eligible patients approached, consented, and enrolled in the study (with reasons for declines recorded)	30 patients randomised to the study protocol over 12 months
Safety	The incidence of Adverse Events (AEs) and Serious AEs (SAEs) associated with SAFEx treatment	An absence of any Serious Adverse Events associated with the study protocol
Retention Rates	Number of participants completing the study protocol versus those who do not (reasons recorded)	≥ 80% of recruited participants complete the study protocol
Acceptability	Participant questionnaires assessing acceptability of the study interventions	Mean VAS scores of ≥ 7/10 for acceptability questions
Exploratory Endpoints—Extubation Failure Rate and EIT Lung Changes	Extubation failure rate at 72 h calculated using electronic medical records Mean global lung impedance measurements calculated for each group at critical points in the extubation and weaning protocol	100% capture of extubation failure rate at 72 h No progression criteria for EIT lung changes as this is an exploratory endpoint

The primary objective of trial recruitment rate will be expressed as the mean monthly recruitment rate over the complete trial period. Additional feasibility outcomes will be expressed in the following ways:Safety outcomes will be expressed as the incidence of AEs or SAEs associated with SAFEx treatment or EIT measurement.Consent rate will be expressed as the number of eligible patients who give informed consent divided by the total number of eligible patients approached.Attrition rate will be expressed in the following ways:◦The withdrawal rate from the study, defined as the number of participants requesting to withdraw from the study due to an inability to tolerate the trial procedures◦The percentage of participants who complete the weaning protocol without breaching any of the physiological patient safety criteria.Retention rate: will be expressed as the number of participants completing the study protocol versus those who do not. Reasons for not completing the study protocol will be recorded.Acceptability outcomes will be expressed as follows:◦Mean patient visual analogue scale scores for questions exploring the acceptability of SAFEx treatment compared with that of standard care.◦Mean patient visual analogue scale scores for questions exploring the acceptability of EIT measurement.Data capture outcomes will be expressed in the following ways:◦The ability to capture the extubation failure rate of patients at 72 h using electronic medical records.◦The ability to capture and calculate the mean global lung impedance measurements for each group at critical points in the extubation and weaning protocol.

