### Ethics and dissemination

#### Safety reporting

Any AEs and SAEs that are identified during trial visits will be assessed, recorded and reported in accordance with the requirements of the trial sponsor.

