#### Trial management

A Trial Management Group consisting of the chief investigator, clinical research fellow and administrative assistant will oversee the running of the trial and meet monthly.

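### Adverse events are summarised only if attributed to SAFEx or EIT, with no all-cause comparison by arm, and Table 3's zero-SAE criterion covers a different event set from its own data cell

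*Protocol article*

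**What the plan says.** The protocol article describes safety in four places.

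- Table 3, safety row, data cell: "The incidence of Adverse Events (AEs) and Serious AEs (SAEs) associated with SAFEx treatment".
- Table 3, safety row, criterion for success: "An absence of any Serious Adverse Events associated with the study protocol".
- The analysis text under the same heading (*Primary feasibility and acceptability data analysis*): "Safety outcomes will be expressed as the incidence of AEs or SAEs associated with SAFEx treatment or EIT measurement".
- Table 2 (*Assessment and measurement*) has one safety endpoint for SAFEx and a separate one for EIT: "The incidence of Adverse Events (AEs) and Serious AEs (SAEs) associated with impedance measurement".

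Three further statements bear on how these will work. *Randomisation* says "Participants will be unblinded to the research team following randomisation". *Safety reporting* says that events identified at trial visits "will be assessed, recorded and reported in accordance with the requirements of the trial sponsor". *Trial management* describes the oversight: "A Trial Management Group consisting of the chief investigator, clinical research fellow and administrative assistant will oversee the running of the trial".

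Where the authors want a comparison with the control arm, they say so. Acceptability is to be given as "Mean patient visual analogue scale scores for questions exploring the acceptability of SAFEx treatment compared with that of standard care", and *Exploratory outcome data analysis* gives reintubation within 72 h as a percentage in each group. No such statement is made for AEs or SAEs.

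**The concern.** There are two linked problems.

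First, an event enters the stated safety summary only after someone has judged it to be associated with SAFEx or with EIT. A standard-care patient does not receive SAFEx, so the SAFEx-associated count has no control-arm counterpart. Serious events are to be expected in recently extubated patients with acute respiratory failure whatever the trial does. Randomisation offers a way to see that background without judging individual events, namely all-cause counts by arm. The plan states this for reintubation but not for AEs and SAEs in general.

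Second, a progression criterion should be decidable from the data listed beside it. Here the data cell, the criterion and the analysis text name three different event sets. One and the same SAE could fail the criterion on one reading and go uncounted on another. The *Discussion* makes meeting the criteria the route to the next, multi-centre feasibility trial, so the ambiguity touches a decision as well as a table.

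**Working it through.** **Inputs.** The maximum sample is 30 patients over 12 months (*Study sample*), and allocation is 1:1 (*Randomisation*), so about 15 receive SAFEx. EIT is applied in both groups (*Group 1*, *Group 2*). The only event rate given is a 15.7% mean extubation failure rate across all critical care patients, which the article thinks is probably higher here (*Study sample*). No SAE rate is given, so the rates below are assumptions.

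**The plan's own figure.** No number is attached to the safety criterion. The figure that sets its denominator does reproduce: 30/12 = 2.5 patients per month.

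**Step 1. Which wording counts which SAE?**

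| SAE | Data cell (SAFEx) | Criterion (protocol) | Analysis text (SAFEx or EIT) |
|---|---|---|---|
| SAFEx patient, attributed to SAFEx | counted | counted | counted |
| Either arm, attributed to EIT | not counted | counted | counted |
| Standard-care patient, attributed to another protocol step | not counted | arguably counted | not counted |
| Either arm, attributed to none of these | not counted | not counted | not counted |

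The second row is the clearest conflict: an EIT-attributed SAE in a standard-care patient fails the criterion, yet the row's own data cell does not collect it. The last row is the all-cause background, which no wording covers.

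**Step 2. How much does the event set change the chance of passing?** With independent patients, a SAFEx-associated SAE risk p in 15 patients and an EIT-associated SAE risk q in all 30:

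- data cell: P(pass) = (1 − p)^15
- SAFEx or EIT: P(pass) = (1 − p)^15 × (1 − q)^30

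For p = 5%, the data cell gives 0.95^15 = 0.463. The wider set gives:

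- q = 0: 0.463
- q = 1%: 0.463 × 0.740 = 0.343
- q = 2%: 0.463 × 0.545 = 0.252

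For p = 10%, the data cell gives 0.90^15 = 0.206.

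**Step 3. How much could attribution matter?** Suppose every reintubation counted as an SAE and occurred at 15.7% (assumption). If all those in the SAFEx arm were attributed to SAFEx, the chance of none among 15 would be 0.843^15 = 0.077. If none were attributed, reintubation could never fail the criterion. The two extremes bracket the effect of a judgement that the article does not define.

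**Step 4. What does zero leave open?** The exact two-sided 95% upper limit for 0/n is 1 − 0.025^(1/n):

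- n = 15: 1 − 0.025^(1/15) = 21.8%
- n = 30: 1 − 0.025^(1/30) = 11.6%

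**Step 5. What would an all-event table by arm add?** It would not give a test. With 15 per arm, power is about 43% for 5% against 30%, and about 27% for 10% against 30%. Its value is to show the background event rate beside the SAFEx rate.

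**The case against.** The other side has several sound points.

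- *Reintubation is compared between arms.* It is reported by group, so a reader cannot say that the plan hides whether reintubation is commoner with SAFEx. This stands, and the point excludes that outcome.
- *The control arm is not wholly left out.* EIT is used in both groups, so EIT-associated events include standard-care patients. The percentage completing weaning without breaching the physiological safety criteria is also stated for participants generally. This stands. What is missing is the all-cause AE/SAE comparison.
- *Nobody is named as the assessor.* A reader might infer from the unblinded design and the internal management group that the unblinded team makes the attribution. The article does not say so. It refers to sponsor requirements, and the full protocol may define causality assessment. The supportable statement is that the trial is unblinded and the article does not define association.
- *Applying one rate to all 30 patients exaggerates.* At 15.7%, 0.843^30 = 0.006, a 0.6% chance of no reintubation in the whole trial. It is tempting to quote this as the chance of passing, but it would require control-arm reintubations to count as protocol-associated SAEs, which no wording says.
- *Any trial of 15 or 30 patients leaves wide limits.* This is true, and the article discloses that its size is resource-driven and below the cited recommendation. It nowhere claims that a pass proves safety. The limits are therefore a reason to report them, not an error.
- *A missed criterion leads to review and modification, not a stop.* This is true and limits the consequences.

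One might add that an article leaves AE table layouts to fuller documents. That answers the absence of detail. It does not answer a published row whose two cells disagree, or a stated form of expression restricted to attributed events.

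**Conclusion.** The point holds in a limited form. As stated, AEs and SAEs are expressed only when associated with SAFEx or EIT. Apart from reintubation, no all-cause comparison with standard care is planned, although the trial is randomised and unblinded and association is undefined in the article. Table 3's safety row is also internally inconsistent, and the analysis text supplies a third event set.

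The size of the inconsistency depends on how likely EIT-associated SAEs are. If they never occur, the data cell and the analysis text give the same result. At an assumed 1% to 2% per patient, with a 5% SAFEx-associated risk, the pass probability falls from 46% to between 34% and 25%. These rates are assumptions; the documents give none.

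This is worth correcting but does not threaten the trial. The *Safety reporting* section says that events identified at trial visits are recorded, so the data for the better summary should exist.

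**What to change.** 1. Use one event set and one denominator in Table 3's data cell, its criterion and the analysis text. One workable choice is SAEs associated with SAFEx or EIT, among all randomised patients. State how association is judged, or point to the document that does.
2. Add a descriptive table of all AEs and all SAEs by randomised arm regardless of attribution: patients with at least one event over patients randomised, with exact 95% confidence intervals and no hypothesis test. Show attributed events in a separate table.
3. Wherever zero events are reported, print the exact two-sided 95% upper limit (21.8% for 0/15, 11.6% for 0/30, recalculated for the actual arm sizes).
4. Keep the zero-SAE criterion.

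*Trial status* says that recruitment has ended and analysis is under way, so the wording change should be dated and declared. The count under each of the three present wordings should be given alongside it.

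The cost is one extra table from events already recorded and a few wording changes. The downside is a less favourable-looking safety statement, because background events in both arms become visible and a zero is shown with its uncertainty.
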